### Intervention: magnesium-based screws

Usual preoperative preparation will be performed. The biodegradable compression screw MAGNEZIX® CS will be used in the following dimensions: MAGNEZIX® CS Ø 2.0 mm, length 8 mm to 24 mm in 2 mm stages, cannulated MAGNEZIX® CS Ø 2.7 mm, length 10 mm to 34 mm in 2 mm stages and cannulated MAGNEZIX® CS Ø 3.2 mm, length 10 mm to 40 mm in 2 mm stages (Fig. 1).

Surgical procedures will be done as established in the study center with minimal access as possible: percutaneous, minimal invasive or open approach depending on the fracture type. After surgery the success of reposition and osteosynthesis will be controlled via plain radiographs. The further treatment and aftercare will be performed strictly as recommended in the AWMF S3 guideline for scaphoid fractures according to the fracture type: no immobilization for stable fractures, 4 weeks of immobilization for waist fractures and 6 weeks of immobilization for proximal pole fractures [6].

According to the fracture type splinting and training will be performed with x-ray control. In case of unclear fracture healing as assessed by x-rays, a CT-scan will be done to determine fracture healing but, according to the AWMF S3 guideline for scaphoid fractures [6] at the earliest 9 weeks after surgery.

### Control: titanium Herbert screws

Usual preoperative preparation will be performed. Classical titanium Herbert screws will be used in the control group. Size of screws and manufacturer are chosen by the surgeon.

All other procedures are identical as in the magnesium group.

### Baseline and follow-up examinations

An overview of scheduled study visits is shown in Table 2. A baseline examination will be prior to surgery after having obtained informed consent. Success of surgery will be checked, in general, at day 1. Wound check is scheduled 2 weeks after surgery. Patients with scaphoid fractures grades B1 to B3 will be seen prior to exercise release. All patients will be seen prior to stress release. Time for exercise and stress release depend on the fracture type (Fig. 2). Before exercise release and before stress release after the period of exercising, clinical examinations will be performed.

**Table 2 Tab2:** Schedule of assessments

	Baseline	Surgery	Success of surgery at day 1	Wound check	Exercise release	Stress release	Follow-up at		
							3 months	6 months	12 months
In- and exclusion criteria	X								
Informed consent	X								
Randomization	X								
Medical history	X								
Medical examination	X	X	X	X	X	X	X	X	X
Adverse events		X	X	X	X	X	X	X	X
EQ-5D-5 L	X						X	X	X
PRWE							X	X	X
DASH							X	X	X
KWS							X	X	X
X-ray / CT (according to guideline)	X		X		X	X	(X)		
Range of motion						X	X	X	X
Grip strength						X	X	X	X
Pain NAS			X	X	X	X	X	X	X

*EQ-5D-5 L* Quality of life; *PRWE* patient-rated wrist evaluation, *DASH* Disabilities of the Arm, Shoulder and Hand, *KWS* Krimmer Wrist Score, *NAS* Numeric analogue scale

**Fig. 2 Fig2:**
[figure not shown]
Trial flow by fracture type. Patients in group A2 start with exercises immediately after surgery, and there is not specific exercise release. Abbreviations used in figure: Consent: informed consent; Rand: randomization; Imag: imaging, i.e., X-Ray and CT-scans according to guideline; Med History: medical history; Med Ex: medical examination; AE: adverse event; Exerc Release: exercise release

Patients will be followed up at 3 months, 6 months and 12 months after randomization. Data will be collected by a physician and a nurse who will both be blind to the randomization status. The follow-up period will 12 months after randomization.

### Magnetic resonance imaging (MRI) group of the trial

Twenty randomized patients from the centers located in or near Hanover – 10 patients with titanium screws and 10 patients with MAGNEZIX® CS – will additionally receive MRI imaging 6 weeks, 3, 6 and 12 months after randomization. MRI scans will be performed on a 3 T scanner located within the MHH.

The scanning protocol will include the following sequences: proton density weighted (PDw) turbo spin echo (TSE) fat saturated (FS) sequences in coronal and axial planes (slice thickness ≤ 2 mm), T2w TSE coronal (1 mm, without FS) and sagittal (≤2 mm, FS), T1w TSE coronal (≤2 mm, without FS) and a T1w TSE oblique sagittal sequence (1 mm, without FS) adjusted to the scaphoid bone. There will be no gap between the slices and the field of view (FOV) will not exceed 10 × 10 cm. No intravenous contrast agent will be used. All images will be viewed in a preset window-level and width with the following values for window center and width (C/W): PDw TSE/T1w 650/1300; PDw WARP 400/800.

### Primary endpoints

Three primary endpoints will be used in this trial. The first primary outcome will be the German version (PRWE-G) of the patient-rated wrist evaluation (PRWE) total score measured 6 months after randomization [32]. The PRWE is a 15-item questionnaire which is completed by the patient. It is a brief, reliable and valid instrument for assessing wrist pain and disability [33, 34]. Scoring for all the questions is on a 10-point ordered scale ranging from ‘no pain’ or ‘no difficulty’ (0) to ‘worst ever pain’ or ‘unable to do’ (10). Two non-overlapping domains pain (5 items) and function (10 items) are generated. Pain and function scores are converted to scales of 0–50 and are summed for a total score, which means that both domains are weighted equally. In case of a missing item, it has been recommended to replace the item with the mean score of the domain.

The PRWE has excellent test-retest reliability, validity and responsiveness [35]. Construct validity was significantly higher in PRWE compared to the short form 36 (SF-36) in patients with distal radius fracture, and it was similar to the DASH [36]. PRWE also outperformed the SF-36 in terms of responsiveness [37]. Overall, Dacombe et al. [35] concluded that the PRWE has by far the best demonstrated reliability and validity in a wrist trauma population among of all the patient rated outcome measures for the assessment of hand and wrist trauma. The PRWE has also been recommended as PRO by others, see, e.g., [38] They also concluded that the PRWE is the most responsive measure for a distal radius fracture population. It is used as primary outcome in at least two ongoing trials (ISRCTN67901257; NCT02154620).

Safety is the second primary outcome. It will be a composite endpoint, consisting of evidence of bone union until 6 months, no adverse device effect (ADE) during surgery, no ADE during wound healing, no reoperation and no serious adverse device effect (SADE) within 1 year after randomization. The outcome “safety event” thus is dichotomous and scored as 1 for a patient ifan ADE occurred during surgery and/oran ADE occurred during the wound healing period and/oran SADE occurred during the 1-year follow-up period and/ora reoperation was performed during the 1-year follow-up period and/orthere was no or incomplete bone union until 6 months after randomization, and 0, otherwise.

AEs during surgery include the following:Nerve events of the superficial division of the radial nerve or the median nerve,vessel events with large hematoma with diameter > 2 cm,screw related complications (fracture or bending of the screw),technical problems (protrusion into the adjacent joint and/or bone without correction, wrong choice of screw length) andrevision of operation technique.

Artifacts will be measured as described by Sonnow et al. [15] to evaluate changes of artifact appearance over time. In detail, all artifacts will be assessed in an axial plane or reconstruction of the screw. In MRI artifacts aligning the y-axis will be considered, defined as the vertical axis of the scanner. As artifact appearance is expected to be symmetrical, measurement will be performed by creating a straight line through the outer boundaries of the artifacts and the central screw axis. The degree of artifact is defined as the diameter of the signal loss induced by the screw in MRI. When artifacts with various lengths are produced, the longest will be measured. This process will be performed in a total of three different axial slices of the screw, and the average value will be obtained. For better orientation and comparability, the artificial cartilage lesion will serve as reference, thus the slices in a similar position will be chosen.

The change in artifacts can now be defined as follows: Difference between maximum length of an artifact between 1-year follow-up and baseline. The third primary endpoint thus is defined quantitatively as the extent of change in artifacts. The specific imaging modality for the third primary endpoint will be defined as early as possible during the trial and before inclusion of the last patient of the MRI part of the trial.

### Secondary endpoints

Secondary endpoints include the domains pain and function of the PRWE, measured at 3, 6 and 12 months. We also use the disabilities of the arm, shoulder and hand (DASH) questionnaire [39] – total score, module scores sport/music, module score work – and the Krimmer wrist score (KWS) with its four domains pain, active flexion/extension arc, grip strength and ability to return to regular employment or activities [40], both measured at 3 months, 6 months and 12 months as secondary endpoints. Range of motion will be assessed with a commercially available goniometer (wrist flexion, wrist extension, wrist radial deviation, wrist ulnar deviation, forearm supination, forearm pronation) at months 3, 6 and 12. At the same follow-up time points, grip strength will be determined with a dynamometer.

Evidence of bone union until 6 months will be determined using x-ray images in 2 planes: anterior-posterior and lateral, in case of uncertainty additionally in a third plane, namely Stecher. Union is defined as complete disappearance of the fracture line on radiographs. If bone healing cannot be assumed in plain radiographs, CT-Scan will be performed according to the AWMF guideline for scaphoid fractures [6]. Images 6 months after surgery will be assessed independently by two experienced radiologists. Edema in MRI will be recorded at 3, 6 and 12 months. Time until return to work and recreational activities will be established through patient self-report.

Finally, quality of life will be measured with the EQ-5D-5 L [41, 42] at baseline, 3, 6 and 12 months after surgery.

### Blinding

Blinded assessment will be done for KWS, range of motion (ROM) and grip strength. Blinding will not be possible for images. The PRWE is patient reported and therefore not assessable in a blinded fashion. In addition, blinding is not possible for the assessment of the effects of the devices for the safety endpoints.

### Randomization

Patients will be randomized individually to one of the two treatment groups in a 1:1 ratio in the order they qualify. After inclusion and exclusion criteria have been checked, the presence of the informed consent form has been ticked and the form has been electronically signed by the surgeon, the randomization result will be displayed in the trial database after anesthesia. Permuted block randomization is used with variable block length stratified by center. Randomization lists for the PBR will be generated using the randomization software RITA [43]. Concealment of allocation will be guaranteed through central randomization within the electronic case report form (eCRF) according to Standard Operating Procedures (SOP).

An expert reviewer pointed out that the trial might have benefited from stratification by fracture type. The decision was to stratify by center because strata would have become very small in case of stratification by center and fracture type. Preference was given to center because of its known effect and its mentioning in the International Conference on Harmonisation (ICH) E9 guideline [44].

### Statistical analysis

All statistical analyses will be described in detail in a statistical analysis plan (SAP) which will be finalized before the randomization of the last patient. Analysis populations for the primary endpoints will be the full analysis set (FAS) based on the intention to treat (ITT) principle and the per protocol population (PP). Neither interim analyses nor adaptations are planned for this trial. All statistical analyses will be done using the R software.

The familywise error rate is set to 5%. The three primary hypotheses will be investigated hierarchically.

The hypothesis for the first primary endpoint is that the mean PRWE in the magnesium-based group is non-inferior to the mean PRWE in the titanium group, measured 6 months after randomization. The non-inferiority margin is 10 points; low values of the PRWE denote ‘no pain’ or ‘no difficulty’. The one-sided 97.5% confidence interval from the t-test will be estimated for judging non-inferiority. Sensitivity analyses will be performed using linear mixed models with center as random effect.

The hypothesis for the second primary endpoint is that the rate of safety events in the magnesium-based group is non-inferior to that in the titanium group within 1 year after surgery. The non-inferiority margin is 15%. The one-sided 97.5% Wilson score interval for the difference of two proportions will be estimated for judging non-inferiority [45]. Sensitivity analyses will be performed using logistic regression mixed models with center as random effect.

The type I error level is set to 2.5% one-sided for the first two primary endpoints. Non-inferiority will only be claimed ifthe hypothesis for the first primary endpoint shows non-inferiority in the FAS based on the ITT population,the hypothesis for the second primary endpoint shows non-inferiority in the FAS based on the ITT population,the hypothesis for the first primary endpoint shows non-inferiority in the PP population andthe hypothesis for the second primary endpoint shows non-inferiority in the PP population.

No adjustments will be made for multiple testing because both tests need to demonstrate non-inferiority.

If non-inferiority has been established, superiority will be tested in the FAS based on the ITT population for the third primary endpoint. The hypothesis for the third primary endpoint is that the mean change in artifact size in MRI between 1-year follow-up and baseline in the magnesium-based group is different from the mean change in artifact size in MRI between 1-year follow-up and baseline in the titanium group. Superiority will be tested at the two-sided 5% test level. The Welch-type t-test will be used for judging superiority at the two-sided 5% test-level.

All secondary endpoints will be tested by appropriate tests and models exploratorily using the two-sided 5% significance level without adjustment for multiple testing.

Missing values for the primary endpoints will be imputed using MICE [46]. Missing data of scores from questionnaires will be handled according to the respective manual. As sensitivity analysis, a complete case analysis will be performed for the primary endpoints.

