### Setting, recruitment, inclusion and exclusion criteria

After diagnosis of a scaphoid fracture and when a decision for the indication of an osteosynthesis with compression screw is made, patients will be recruited by the surgeon in 13 high-volume centers in Germany. Each center has experience in conducting clinical trials, treating patients with scaphoid fractures and the use of both MAGNEZIX® CS compression screws and titanium Herbert screws. All surgeons are trained in fixation of scaphoid fractures with titanium Herbert screws and MAGNEZIX® CS compression screws prior to the trial.

Study centers will receive a case payment of 500 € in two parts. The first payment in the amount of 50% will be paid after surgery and the second part after 12 months, if complete follow-up data is available.

Inclusion and exclusion criteria are displayed in Table 1.

**Table 1 Tab1:** Inclusion and exclusion criteria

Inclusion criteria: • Indication for screw fixation of scaphoid fracture which is not older than 12 weeks; classification by Herbert, modified by Krimmer of types A2, B1, B2, B3 [4], • normal wrist function prior to fracture, • age ≥ 18 years, • written informed consent for trial participation and surgery. Exclusion criteria: • Previous surgery on the wrist, associated injuries, state after or suspicion of complex regional pain syndrome (CRPS), • simultaneous fractures of the forearm of both sides and those who will influence the postoperative care, • known ligamentary concomitant injuries of the wrist on both sides and those who will influence the post-operative care, • radiological findings of medium to high grade osteoporosis, • intended or conducted spongiosa transplantation or bone graft transplantation during surgery, • pregnancy, suspected pregnancy or breastfeeding period, • allergies to components of osteosynthesis material, • participation in other clinical trials up to 30 days before inclusion in this trial, • central neurological deficits which do not permit a compliance to the trial, especially during follow-up, • for patients recruited to the centers near Hanover and undergoing MRI: claustrophobia and metallic implants which are contraindicative for an MRI.	

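### The decisive PRWE interval ignores center although randomization is stratified by center: valid and slightly conservative, and easily aligned with the design

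*Protocol article*

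**What the plan says.** Under Randomization, the protocol article states: "Permuted block randomization is used with variable block length stratified by center". It explains why center was chosen over fracture type: "Preference was given to center because of its known effect and its mentioning in the International Conference on Harmonisation (ICH) E9 guideline". Under Setting, recruitment, inclusion and exclusion criteria, it gives the number of strata: "patients will be recruited by the surgeon in 13 high-volume centers in Germany".

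Under Statistical analysis, the rule for PRWE at 6 months is: "The one-sided 97.5% confidence interval from the t-test will be estimated for judging non-inferiority". The margin is 10 points. Center appears in the sentence on sensitivity analyses: "Sensitivity analyses will be performed using linear mixed models with center as random effect".

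Safety follows the same pattern with a margin of 15%: "The one-sided 97.5% Wilson score interval for the difference of two proportions will be estimated for judging non-inferiority", and then "Sensitivity analyses will be performed using logistic regression mixed models with center as random effect". The four conditions for claiming non-inferiority (both endpoints, each in the FAS and in the PP population) do not include the sensitivity analyses.

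**The concern.** The design treats center as prognostic and the decisive PRWE analysis treats it as ignorable. Stratified blocks make the two groups nearly balanced within each center, so center differences largely cancel from the difference in means. The two-sample t interval still carries those differences in its standard error. Its stated precision therefore does not match the design, and the upper limit sits somewhat further out than it needs to.

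At stake is a little precision on an endpoint that must succeed in both the FAS and the PP population before anything can be claimed. The center-adjusted model is already planned and is on the points scale, so nothing prevents it from being the decisive analysis.

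**Working it through.** **Inputs from the protocol article.** Margin 10, SD 20, true difference 0, one-sided level 0.025, power 0.9, drop-out 10%, 13 centers, and a safety rate of 0.9 in both groups with margin 0.15. **Assumed, because not given:** the intra-center correlation (ICC) of PRWE, from 0 to 0.20; the between-center SD of the safety event rate, from 0 to 0.10; and block lengths of 4 and 6.

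**1. The plan's own figures.** PRWE: n per group = 2 × (1.960 + 1.282)² × 20² / 10² = 84.06, and 84.06 / 0.9 = 93.4, rounded up to 94. This is the stated figure. Safety: Φ(0.15 / √(2 × 0.9 × 0.1 / 86) − 1.960) = 90.64%, also as stated. Neither calculation has a center term, so the trial was sized for the unadjusted analysis.

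**2. Formula for PRWE.** Removing center leaves a residual SD of 20 × √(1 − ICC). Power with 85 evaluable per group is Φ(10 / (SD × √(2/85)) − 1.960). This is an upper bound on what adjustment offers, because it assumes perfect balance within centers and no loss of degrees of freedom.

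**3. Simulation for PRWE.** Permuted blocks in 13 centers, with center as fixed effects in the adjusted analysis. One set-up has near-equal centers and 170 evaluable patients. The other has unequal centers and 10% drop-out. Entries are power in %, unadjusted / adjusted.

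| ICC | Residual SD | Formula, adjusted | Equal centers | Unequal centers |
|---|---|---|---|---|
| 0 | 20.0 | 90.3 | 90.3 / 90.1 | 89.9 / 89.3* |
| 0.02 | 19.8 | 90.9 | not run | 89.9 / 89.7 |
| 0.05 | 19.5 | 91.7 | 90.3 / 91.2 | 90.2 / 90.8 |
| 0.10 | 19.0 | 93.0 | 90.8 / 92.5 | 91.1 / 92.5 |
| 0.20 | 17.9 | 95.4 | 92.1 / 94.9 | 92.6 / 94.9 |

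*From a separate run of the same kind.

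With unequal centers, adjustment changes power by 89.7 − 89.9 = −0.2, 90.8 − 90.2 = +0.6, 92.5 − 91.1 = +1.4 and 94.9 − 92.6 = +2.3 points at ICC 0.02, 0.05, 0.10 and 0.20. With equal centers the gains at 0.05, 0.10 and 0.20 are 0.9, 1.7 and 2.8 points.

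**4. Type I error for PRWE at the margin.** With perfect balance, the unadjusted one-sided error would be Φ(−1.96 / √(1 − ICC)): 2.2% at ICC 0.05 and 1.9% at 0.10. Incomplete blocks weaken this. With equal centers the simulated error is 2.4%, 2.4%, 2.2% and 1.5% at ICC 0, 0.05, 0.10 and 0.20. With unequal centers it is about 2.3% at 0.05 and 0.10. In the equal-center runs the adjusted analysis stays at 2.4% to 2.7%.

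**5. Safety.** 170 / 13 ≈ 13 evaluable patients per center, and at a 10% event rate about 1.3 events each. Power of the unstratified Wilson-type (Newcombe) interval against a stratified Newcombe interval with Mantel-Haenszel weights was 88.0 / 87.0%, 88.3 / 87.4% and 88.9 / 88.4% for between-center SDs of 0, 0.05 and 0.10. A second simulation gave 87.7 / 87.0%, 88.0 / 87.5% and 88.2 / 87.9%. A Mantel-Haenszel difference with Sato variance had power of 89.4% to 92.1%, but at a one-sided error of 2.9% to 3.6%. For the unstratified interval, separate equal-center runs gave errors of 2.7%, 2.5% and 2.1%.

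**6. Scale of the safety sensitivity model.** A 15-point excess corresponds to an odds ratio of ((p + 0.15) / (0.85 − p)) / (p / (1 − p)), that is 4.75, 3.00, 2.43 or 2.15 at control event rates p of 5, 10, 15 or 20%. No single odds-ratio margin follows from 15 points.

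**The case against.** The strongest reply is that nothing here is an error. The unadjusted interval is valid, it leans in the safe direction for a non-inferiority claim, and the sample size was computed for exactly that analysis, so about 90% power is delivered. The gain from adjustment depends on a correlation that the article does not give, and below an ICC of about 0.05 it is indistinguishable from zero. All of this stands. It limits the size of the point, but it does not remove the mismatch between how patients are allocated and how the decisive comparison is made.

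Three stronger readings are tempting and not supported.

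- A reader might infer that power is lost on both primary endpoints. For PRWE, what is forgone is a small bonus above the planned power. For safety, the stratified Newcombe interval shows no gain, and the Mantel-Haenszel alternative gains only with a type I error above the nominal level.
- A reader might infer that the center-adjusted safety analysis cannot be read against the margin. The article names a logistic mixed model but does not say that an odds ratio will be reported. A risk difference can be derived from that model, and the choice can properly be left to the SAP, which is not shown.
- A reader might infer that leaving out fracture type costs further precision. The article explains why it was not a stratification factor and gives no figure for its prognostic value.

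**Conclusion.** The point holds for PRWE as a modest improvement to a stated method. Center was put into the design for its effect and should be in the decisive PRWE model. The benefit is roughly 0 to 1.5 points of power for an ICC of 0.02 to 0.10, and 2 to 3 points at 0.20. The unadjusted one-sided error is about 2.2% to 2.4% at an ICC of 0.05 to 0.10. The false non-inferiority rate is not materially inflated under either analysis.

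These figures rest on assumed ICCs, on block lengths of 4 and 6, and on fixed center effects in the simulations rather than the planned random effect. For safety, the unstratified interval is the sound choice with strata this sparse.

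**What to change.** - **PRWE.** Make the planned linear mixed model with treatment and a random center effect the primary analysis in both the FAS and the PP population. Non-inferiority is judged by comparing the upper one-sided 97.5% limit for magnesium minus titanium with 10 points. The two-sample t interval becomes the sensitivity analysis.
- **Safety.** Keep the unstratified Wilson interval as decisive. State in the SAP that the logistic mixed model will be reported as a standardized risk difference with its interval, set beside the 15-point margin.

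The cost is wording in the protocol and the SAP, which by the article's own schedule is finalized before the last patient is randomized, and a few lines of R. No patients or data are added. The downside is a negligible loss of precision if center has no effect: 0.2 to 0.6 points of power in the simulations with fixed center effects.

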### Sample size calculations

Aim of the trial is to demonstrate non-inferiority of magnesium-based compression screws when compared with titanium Herbert screws for the fixation of scaphoid fractures. Standard deviations (SD) for the PRWE in the literature were all approximately 20 points [47]. Lange and Freitag [48] reported in their systematic review that many studies used a non-inferiority margin of 0.5 SD. This limit is used a non-inferiority margin for the planning of the scaphoid trial for the primary endpoint PRWE. This leads to the following assumptions for the sample size calculations for the first primary endpoint: Allocation ratio 1:1, type I error level 0.025 one-sided, power 0.9, expected difference between titanium and magnesium-based screws: Δ_1_ = 0, common standard deviation: σ = 20, non-inferiority margin: Δ_0_ = 10, drop-out 10%. To demonstrate non-inferiority under these assumptions, 94 patients per group, i.e., 188 patients in total are required for this trial.

If non-inferiority has been established for the first primary endpoint, the power to establish non-inferiority for the second primary endpoint, the safety endpoint is 90.64% under the following assumptions: type I error level 0.025 one-sided, event rate for magnesium-based and titanium screws: 0.9, non-inferiority margin: Δ_0_ = 0.15, drop-out 10%.

If non-inferiority has been established for the first primary endpoint and the second primary endpoint, the power to establish superiority for the third primary endpoint, the change in artifacts endpoint is virtually 100% under the following assumptions: type I error level 0.025 one-sided, expected difference between titanium and magnesium-based screws: Δ_1_ = 3.0, common standard deviation: *σ* = 1.0, sample size per group: *n*_*A*_ = *n*_*B*_ = 10, drop-out 10%, effective sample size per group: *n*_*A*_ = *n*_*B*_ = 9. The power is 56.41% if the mean difference is Δ_1_ = 1.0 instead of Δ_1_ = 3.0, and it is approximately 80% for Δ_1_ = 1.32.

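### Optional gain, not an error: the PRWE non-inferiority limit could come from a model with baseline EQ-5D-5L and center, both already recorded, instead of an unadjusted t interval

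*Protocol article*

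**What the plan says.** Under Statistical analysis, the protocol article fixes how the first primary endpoint is decided: "The one-sided 97.5% confidence interval from the t-test will be estimated for judging non-inferiority". The margin is stated in the same paragraph ("The non-inferiority margin is 10 points; low values of the PRWE denote" few complaints), so the upper limit for magnesium minus titanium has to fall below 10 points. The only model named for this endpoint is secondary to that: "Sensitivity analyses will be performed using linear mixed models with center as random effect". Neither analysis names a baseline covariate.

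Table 2 (Schedule of assessments) starts the PRWE, DASH and Krimmer score at 3 months and the pain scale at day 1 after surgery. The EQ-5D-5L is the only patient-reported instrument marked at baseline, and Secondary endpoints agrees: "quality of life will be measured with the EQ-5D-5 L [41, 42] at baseline, 3, 6 and 12 months after surgery". Baseline is before surgery, and under Randomization the allocation is shown only after anesthesia. That section also explains that center was chosen as the stratification factor because its effect is known.

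**The concern.** The usual covariate for a patient-reported outcome is the same score at baseline. Here it does not exist, because no PRWE is scheduled before 3 months. One other patient-reported score is taken at baseline, before the allocation is disclosed, and the decisive analysis does not use it. Nor does that analysis use center, the factor on which randomization is stratified.

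A covariate that predicts the outcome narrows the interval. That has some value here because the overall claim is demanding: non-inferiority must be shown for both PRWE and safety, each in the full analysis set and the per protocol population, and the MRI comparison is tested only afterwards. The stated power is 0.9 for PRWE and 90.64% for safety. If the two were independent (an assumption), their joint power would be 0.90 × 0.9064 = 0.816 before the per protocol requirement is added. Any gain on PRWE carries through to that product.

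**Working it through.** **Inputs from the article.** Error level and target power: "type I error level 0.025 one-sided, power 0.9, expected difference between titanium and magnesium-based screws", the last being 0. Allocation: "Allocation ratio 1:1". Variability: "Standard deviations (SD) for the PRWE in the literature were all approximately 20 points". Margin: 10 points. Stated result: "drop-out 10%. To demonstrate non-inferiority under these assumptions, 94 patients per group, i.e., 188 patients in total are required for this trial".

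**Input not in the article.** r, the within-arm correlation between baseline EQ-5D-5L and 6-month PRWE. It is an assumption, shown from 0 to 0.4.

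**Step 1: reproduce the plan's figure.** Per arm, n = 2 × (1.960 + 1.282)² × 20² / 10² = 84.06, rounded up to 85. With dropout added as 85 × 1.1 = 93.5, this gives 94 per group and 188 in total, as stated. (Dividing by 0.9 instead would give 94.4, that is 95.)

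**Step 2: the planned unadjusted analysis, 85 evaluable per arm.**
- Standard error = 20 × √(2/85) = 3.068 points.
- Degrees of freedom = 168; critical t = 1.974.
- Distance from estimate to limit = 1.974 × 3.068 = 6.06 points.
- Noncentrality = 10 / 3.068 = 3.26; power from the noncentral t distribution = 89.99%.

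So the planned analysis is on target under its own inputs.

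**Step 3: adjust for baseline EQ-5D-5L.** The residual SD becomes 20 × √(1 − r²), and one degree of freedom is lost (167 remain).

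| Assumed r | Residual SD | Distance to limit (points) | Power, 85 per arm | Evaluable n per arm for 90% power |
|---|---|---|---|---|
| unadjusted | 20.00 | 6.06 | 90.0% | 86 |
| 0.1 | 19.90 | 6.03 | 90.3% | 85 |
| 0.2 | 19.60 | 5.93 | 91.1% | 82 |
| 0.3 | 19.08 | 5.78 | 92.5% | 78 |
| 0.4 | 18.33 | 5.55 | 94.3% | 72 |

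(The last column uses the t distribution, hence 86 and not 85 in the first row.)

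**Step 4: the price if the covariates predict nothing.** At r = 0, losing one degree of freedom leaves power at 89.99%. Center costs more if entered as fixed effects: 13 centers take 12 further degrees of freedom, so 168 − 1 − 12 = 155 remain. The critical t rises from 1.974 to 1.975 and power is 89.96%. This takes the arms as balanced within centers, which the stratified blocks should roughly achieve. Any gain from center comes on top of the table but cannot be sized, because the article gives no between-center variance.

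**Step 5: effect on the joint claim.** Under the same independence assumption, 0.816 becomes 0.911 × 0.9064 = 0.826 at r = 0.2 and 0.925 × 0.9064 = 0.838 at r = 0.3.

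**The case against.** The strongest reply is that there is nothing to correct. A two-sample t interval is valid under randomization, its error rate already allows for chance imbalance, and it matches the sample-size calculation exactly. That stands in full, and it is why the point is offered only as an improvement.

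The second reply is that r may be small. Baseline is taken after the fracture, in patients whose wrist function was normal before it and whose fracture may be up to 12 weeks old. A generic quality-of-life score at that moment describes the current injury at varying times since it happened, and it need not predict wrist function 6 months later. This also stands: at r of 0.2 or below the gain is about one power point or less. What remains is that the downside is close to nil.

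The third reply is that, if the primary model is to be adjusted, center is the covariate the article itself supports. That is right, and the proposed model therefore includes center along with the EQ-5D-5L.

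Two stronger readings should be resisted. A reader might infer that the plan throws away precision it has already paid for; the article gives no correlation from which to show that any material precision is lost. A reader might also infer that adjustment protects an unblinded, patient-reported endpoint. It does not: adjusting for a baseline score cannot remove bias in how patients report at 6 months once they know their implant.

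**Conclusion.** The facts hold: the decisive PRWE interval is unadjusted, no baseline PRWE is scheduled, and one baseline patient-reported score and the stratification factor are left out of that interval. The consequence is modest and uncertain: between nothing and about 4 power points for r from 0 to 0.4, and about 1 point or less if r is 0.2 or lower. These figures assume SD 20, true difference 0, margin 10, 85 evaluable patients per arm and a linear relation with the same slope in both arms. This is a low-priority suggestion; leaving the analysis as it is would not invalidate the trial.

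**What to change.** Under Statistical analysis, state that the one-sided 97.5% limit for the PRWE difference at 6 months comes from a prespecified linear model with treatment, baseline EQ-5D-5L index and center, in both the full analysis set and the per protocol population. Say whether center enters as a fixed or a random effect. Keep the 10-point margin and the present sample size, and report the unadjusted t interval as a sensitivity analysis beside the one with center as random effect.

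The cost is wording, plus a rule for a missing baseline EQ-5D-5L. No new data, visits or patients are needed. The article says the analysis plan will be finalized before the last patient is randomized; the change should be made by then and without sight of outcome data by arm.
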